Visit 2 will occur 25–35 days postpartum in clinical research facilities at Nationwide Children’s Hospital in Columbus, Ohio (Table 2). Body measurements, including weight, will be repeated. A registered nurse will collect biomarker measurements of insulin resistance via venipuncture, including a fasting 2-h, 75 g oral glucose tolerance test (OGTT); insulin; hemoglobin A1c; lipid panel; adiponectin; leptin; and high sensitivity C-reactive protein. A point-of-care glucose test will be performed at the beginning of each visit and will have a threshold of 250 mg/dL; if a participant’s fasting glucose is above the threshold, the principal investigator and registered nurses will investigate the situation to determine whether the participant should be withdrawn or rescheduled. The body composition and biomarker measurements completed at this visit will serve as the baseline measures. All Visit 1 questionnaires will be completed for a second time with the addition of the Diet History Questionnaire III (DHQ III). All participants will wear the ActiGraph wGT3X-BT accelerometer for 21 days after Visit 2 to monitor activity and energy expenditure. Study staff will share all blood test results with the participant and their OB/GYN or primary care provider via a letter sent in the mail stating that the results were collected for a research study and that the research staff will not provide follow-up care. Study staff will encourage participants to follow-up with their providers to discuss their results.

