### Primary outcome

#### Weight loss

The Tanita TBF-310GS Body Composition Analyzer will measure weight. Women will be weighed wearing light clothing and no shoes nor socks. We will account for 1 kg of clothing weight for every participant during each measurement. Postpartum weight loss will be defined as weight change between Visits 2 and 3.

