### Analysis

The study will adhere to CONSORT statement guidelines using intent-to-treat as the primary approach for analysis. All individuals will be kept in the group to which they were randomized, regardless of protocol violations or dropouts. Only the pre-specified covariates of baseline outcome variable, race, pre-pregnancy BMI category, GDM severity, parity, clinic location, and education will be included as covariates in the primary and secondary analyses unless imbalances are detected across arms in baseline variables [32]. Balance between the treatment groups will be tested by informally comparing baseline variables between study arms. Outliers will be checked and kept in the final analysis. Outcome variables will also be examined over time at the group and the individual level graphically as well as via descriptive statistics stratified on time and group. No interim analyses or stopping guidelines are planned regarding data monitoring.

Furthermore, bivariate relationships between outcome variables and potential covariates will be examined to determine if substantial deviations from linearity exist. We will make an effort to minimize dropouts and missing data, but if substantial missing data is realized, maximum likelihood estimation will be employed. Although not expected, if substantial non-compliance is realized, modern methods for handling missing data will be utilized [33, 34]. We will continue to collect all outcome data from participants who discontinue the intervention as long as the participant does not formally withdraw and is not lost to follow-up.

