Analyses for the primary and secondary outcomes will involve a mixed effects model for repeated measures, similar to ANCOVA but based on maximum likelihood [35]. The same approach, statistical models, and time points (i.e., Visit 2 and 3) used for our primary hypothesis will be used for our secondary hypotheses, with each body composition and biomarker outcome in separate models instead of weight loss. For the Exploratory Aim, we will employ a longitudinal mediation model with multiple mediators. We will use Mplus 7.31 with bootstrapping procedures to statistically test mediators. We will follow the guidelines for testing longitudinal mediation within Cole and Maxwell and MacKinnon [36, 37]. These tests are important for clinical applicability of the intervention by identifying the most salient mechanisms of change that ultimately lead to better outcomes in our target population. Multiple publications will be submitted to peer-reviewed journals to disseminate study results.

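### The Analysis section, read with the baseline definition, puts Visit 2 weight in the primary mixed model both as a repeated response and as a covariate, and names no treatment contrast

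*Protocol article*

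**What the plan says.** Four statements in the Protocol article bear on this.

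- **Baseline.** The Visit 2 section says of that visit: "The body composition and biomarker measurements completed at this visit will serve as the baseline measures". Weight is among the body measurements repeated there.
- **Outcome.** The Weight loss section says: "Postpartum weight loss will be defined as weight change between Visits 2 and 3".
- **Covariates.** The Analysis section says: "Only the pre-specified covariates of baseline outcome variable, race, pre-pregnancy BMI category, GDM severity, parity, clinic location, and education will be included", for both the primary and the secondary analyses.
- **Model.** The Analysis section specifies "a mixed effects model for repeated measures, similar to ANCOVA but based on maximum likelihood". It then carries the same approach, and the "time points (i.e., Visit 2 and 3) used for our primary hypothesis", over to every body composition and biomarker outcome.

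The article gives no covariance structure and does not say which model term is the treatment effect. The nearest indication is in the Participants section, where the sample size rests on how the arms' mean weights differ in their course from baseline to endpoint, and on mean weight change.

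**The concern.** With only two time points, a model has repeated responses only if Visit 2 is one of them. Visit 2 is also the baseline, and the baseline outcome is a covariate. So on the natural reading the Visit 2 response equals its own covariate. For weight, where the slope on baseline is close to 1, the Visit 2 rows then have residuals near zero.

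A model with one common residual variance averages that near-zero variance with the real variance at Visit 3. A group effect taken over both visits averages a zero difference before randomisation with the real difference at the end. At stake are the size of the reported primary effect or the validity of its standard error. Because the model is shared, the same holds for every secondary outcome.

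**Working it through.** **The plan's own figure.** For d = 0.50, 80% power and two-sided alpha 0.05 (alpha and sidedness are assumed), the normal approximation gives 2 × (1.960 + 0.842)² / 0.50² = 62.8, so 63 per group. The t-test gives 64 per group with power 80.1%. Then 64 / 0.80 = 80 per group, 160 in total. The stated sample size reproduces.

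**Inputs**
- From the Participants section: pilot losses of 6.3 and 3.9 lb, so a difference of 2.4 lb = 1.09 kg; pilot d = 0.63; design d = 0.50; 80 per arm; 20% drop-out, leaving 64 per arm at Visit 3.
- SD of change (not stated): 1.09 / 0.63 = 1.73 kg if the pilot d is scaled on change, or 1.09 / 0.50 = 2.18 kg. Both were used.
- Assumed, with no source in the article: Visit 2 weight SD 18 kg, and a slope of change on baseline of -0.03.

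**Analytic check.** Take Visit 2 residuals as zero and the Visit 3 residual variance as σ². Over both visits there are 160 + 128 = 288 rows, so the pooled variance is about (128/288)σ² = 0.444σ².
- *Group main effect.* The share of rows from Visit 3 is 128/288 = 0.444, so the expected estimate is 0.444 × 1.09 = 0.48 kg. Without drop-out the share is 0.5, giving 0.55 kg.
- *Group-by-time.* The model variance is 0.444σ² × (2/64 + 2/80); the true variance is σ² × 2/64. The SE ratio is √(0.444 × 0.05625 / 0.03125) = √0.8 = 0.894. The two-sided error at 1.96 × 0.894 = 1.753 is 8.0%. Without drop-out the ratio is √(0.5 × 2) = 1.
- *Visit 3 contrast, common variance.* The SE ratio is √0.444 = 0.667, so the error is 19%. Without drop-out it is √0.5 = 0.707, so 17%.
- *Unstructured covariance with one baseline slope.* The Visit 2 residual is exactly zero at slope 1, so the likelihood is degenerate.

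**Simulation.** There were 4,000 trials per cell with 80 per arm. The stacked model was fitted by least squares, which is the random-intercept model with its intercept variance at zero. Results for an SD of change of 2.18 kg:

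| Analysis | Mean estimate, 20% drop-out (true 1.09 kg) | Model SE / empirical SE (no true effect), 20% drop-out | Type I error, 20% drop-out | Type I error, no drop-out |
|---|---|---|---|---|
| Group main effect | 0.49 | 0.174 / 0.173 | 4.5% | 4.9% |
| Group-by-time | 1.10 | 0.350 / 0.399 | 8.6% | 5.4% |
| Visit 3 contrast, common variance | 1.10 | 0.261 / 0.393 | 19.1% | 15.5% |
| ANCOVA, Visit 3 on Visit 2 | 1.10 | 0.386 / 0.390 | 5.0% | 5.1% |

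With an SD of 1.73 kg the drop-out type I errors were 5.2%, 8.5%, 18.7% and 5.9%, so the pattern does not depend on that choice.

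**Secondary outcomes.** With complete data the group-by-time SE ratio is √((3 + ρ)/4), where ρ is the correlation between Visits 2 and 3. It is 0.999 at ρ = 0.995 (about that of weight), 0.987 at 0.9 and 0.94 at 0.5. At ρ = 0.5 the simulated type I error was 6.8%, before any drop-out.

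**The case against.** The best defence is that the text allows a reading without double use. The Analysis section calls the primary response weight loss, which the Weight loss section defines as the change between the two visits. The two time points may then simply say which visits form the change, with Visit 2 weight as the covariate, hence the comparison with ANCOVA. That model is sound. But nothing in it is repeated, so the stated model type would be wrong. This reading shows that the text needs reconciling; it does not remove the conflict.

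A reader might infer that the primary effect is bound to be halved, or its standard error bound to be wrong. The article does not support that. It writes no contrast and no covariance structure, and such detail may sit in a separate analysis plan. The sample size text points to group-by-time, which is not halved and which for weight is close to nominal without drop-out. Where the effect is halved, its SE shrinks too, so the test is nearly preserved. A degenerate unstructured fit would probably show itself as a fitting failure.

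A reader might also see a contradiction between maximum likelihood as the general method and the sentence "if substantial missing data is realized, maximum likelihood estimation will be employed". The two barely conflict, since both lead to maximum likelihood. The condition is merely unnecessary.

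**Conclusion.** The specification conflict is real: Visit 2 is the baseline, the baseline outcome is a covariate, and Visit 2 is one of two time points in a repeated-measures model. The harm is conditional on the contrast and covariance chosen:

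- group main effect: about half the true difference, test nearly preserved;
- group-by-time: unbiased, SE about 10-12% too small with 20% drop-out, type I error about 8-9%;
- Visit 3 contrast under a common variance: type I error about 15-19%, depending on drop-out;
- unstructured covariance: degenerate.

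The sizes rest on the assumed Visit 2 SD of 18 kg, an SD of change of 1.73-2.18 kg, two-sided alpha 0.05, drop-out unrelated to outcome, and an intercept variance estimated at zero. The sample size is unaffected. It follows from d = 0.50 on a two-group comparison, and ANCOVA with 64 per group holds at least that power (80% at ρ = 0.995, 90% at ρ = 0.5).

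**What to change.** Use Visit 2 weight once, and state one of these models:

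1. ANCOVA of Visit 3 weight (or of the change, which gives the same treatment estimate) on Visit 2 weight plus the other listed covariates; or
2. a constrained longitudinal model with Visit 2 and Visit 3 weight as responses, a common baseline mean across arms, unstructured covariance, the other listed covariates, and no baseline-outcome covariate. This also keeps women who have Visit 2 but no Visit 3, in line with the intention-to-treat statement.

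Name the between-group difference at Visit 3 (equivalently, in change from Visit 2) as the treatment effect. Apply the same model to each secondary outcome. Use likelihood estimation whatever the amount of missing data, and delete the condition about substantial missingness.

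The cost is a few sentences in the protocol or analysis plan, settled before the outcome data are analysed. No new data are needed and the sample size does not change.

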### Participant safety and monitoring and data management

Human subjects review and approval are under the Nationwide Children’s Hospital’s Institutional Review Board (IRB) with a reliance agreement from the Ohio State University Medical Center’s IRB. The IRB has deemed the study “minimal risk.” Experienced research nursing staff will perform biospecimen collections and monitor patients during oral glucose tolerance tests. Study staff will assess adverse events at each study visit and during each data collection call via online surveys using REDCap software. The principal investigator and study doctor will review the adverse events monthly unless suspected to be Serious Adverse Events, and they will determine what action will be taken due to the adverse event regarding the study intervention. The study investigators will inform the IRB of all adverse events and will report all serious and related adverse events on an expedited timeframe per IRB guidelines.

The study will follow all necessary measures to assure the participant data stored in the database are protected and secure from unauthorized access. Only team members who are approved by the IRB to have access to the data will have access. Data use agreements with external collaborators may be possible as long as they are within the scope of the informed consent form. There is no planned auditing from the funder or other outside entity. Internal audits may be conducted on an unannounced basis.

## Discussion

The Moms in Motion study is innovative in its emphasis on simplicity to accelerate health improvement during a time when attention to self-health is not easily attainable. All new mothers experience physical and lifestyle changes and unavoidable time constraints postpartum, making it challenging to initiate sustainable weight loss efforts, which are essential for women with GDM to prevent/delay a T2DM diagnosis. The occurrence of GDM and high postpartum weight retention [1] continually contribute to the increasing number of women with T2DM. This study was designed to test an intervention to reduce T2DM risk among women who had GDM by considering the postpartum demands new mothers experience.

By testing an intervention that is sensitive to the postpartum demands new mothers experience, requiring minimal time and effort, we can shift current clinical paradigms to facilitate early weight loss and reduce T2DM risk among women with GDM. Beyond the expectation of this study to be significant in its direct health impacts from weight loss, it will be significant in exploring (1) the mechanism(s) by which the intervention is successful (mediating effects of energy expenditure and/or diet on weight loss) and (2) the effects of the intervention on body composition and biomarkers associated with insulin resistance and metabolic health.

Although this study is ongoing, we will expect the findings to be meaningful regarding the effectiveness of the intervention and how to engage women with GDM in the postpartum period to reduce T2DM risk. A limitation of this study is that we lack the resources to translate and validate questionnaires and other materials into other languages, so we must exclude women who do not speak English, which may reduce the generalizability of the findings. Also, participants will be followed to 12 months’ postpartum, but current resources do not permit longer-term follow-up. Future directions could incorporate following the participants over an extended period, beyond the duration of this study, to observe continued or sustained weight loss. Future research could also involve conducting a similar intervention in other settings or with larger samples adequately powered to robustly examine mechanisms.

## Data Availability

Not applicable.

## Abbreviations

GDM: Gestational diabetes mellitus
T2DM: Type 2 diabetes mellitus
OGTT: Oral glucose tolerance test
DPP: Diabetes Prevention Program
RCT: Randomized controlled trial
PI: Principal investigator
IRB: Institutional Review Board
